## Abstract

**Introduction::**

Allergic rhinitis (AR) is a major chronic inflammatory disease of the respiratory tract. A large number of epidemiological investigations have shown that the prevalence of AR is increasing, resulting in a large social burden. Importantly, the impact of air pollution on health is a widespread concern. We aim to evaluate association of air pollution and AR risk.

**Methods and analysis::**

This prospective study includes patients undergoing AR. The exclusion criteria will be as follows: Patients with nasal infection, nasal polyps, nasal tumors, mental disorders, and immunodeficiency will be excluded. Air pollution levels of ambient air pollutants including PM2.5, PM10, sulfur dioxide (SO_2_), nitrogen dioxide (NO_2_), carbon dioxide (CO), and O_3_, and patient data will be collected. The correlation analysis will be performed in air pollutants and AR risk.

**Discussion::**

This study will provide correlation of NO_2_, SO_2_, PM10, and PM2.5 for AR in several aspects, including symptom score, drug score, quality of life score, asthma control score, side effects, and laboratory examination such as nasal function test, serum total immunoglobulin E, and nasal secretion smear.

## Introduction

1

Rapid economic development and the acceleration of urbanization have aggravated the haze in Sichuan, including Deyang city, an important industrial city in north Sichuan. The impact of air pollution exposure on human health has become a sensitive topic for the public, media, and even the government in China and neighboring countries.^[1]^ To evaluate the impact of outdoor air pollution on human health and implement appropriate protection policies, relevant studies have been conducted in the past decades.^[2,3]^ Many adverse health problems have been reported associated with air pollution, including respiratory diseases (rhinitis, asthma, bronchitis, and pneumonia),^[4]^ cardiovascular diseases (stroke, cardiac arrhythmias, and ischemic heart disease),^[5]^ chronic obstructive pulmonary disease (COPD),^[6]^ more rarely, conjunctivitis,^[7]^ skin disease,^[8]^ and cough.^[9]^ Researches on the correlation between air pollution and respiratory diseases (such as asthma and COPD) are abundant,^[6]^ while few studies investigated the correlation of allergic rhinitis (AR) with air pollution in China.

The AR is a noninfectious respiratory inflammatory disease of nasal mucosa mediated by immunoglobulin E.^[10]^ Moreover, AR involves a variety of immune-active cells and cytokines after atopic individuals are exposed to allergens, affecting 10% to 40% in the world.^[11]^ In China, the prevalence rate of adults is about 4% to 38%.^[12]^ Due to the easy relapse of AR and the delay in the course of the disease, the life, and work of the patients has been seriously affected. Some AR patients have suffered from asthma,^[13]^ nasal polyps, and rhinosinusitis.^[14]^ Obviously, AR has become a public health problem. Some experts believe that the increase in the prevalence of AR is caused by the increase of air pollutants^[15–19]^; however, there is still no hard evidence to support it. At present, there are no continuous and dynamic studies to observe the changes of pollutants and the AR risk.

This study was designed to assess the relationship between air pollution exposure and the risk of AR.

## Methods and analysis

2

### Main aims

2.1

We aim to clarify the relationship between air pollution exposure and the risk of AR. Flow chart of study protocol is shown in Figure 1.

**Figure 1 F1:**
[figure not shown]
Flow chart of study protocol. AR = allergic rhinitis, CO = carbon dioxide.

#### Special aim

2.1.1

Aim 1: By collecting the general clinical data of patients with AR in multicenter outpatient clinics in Deyang region from January 2019 to December 2020, the prevalence of AR in outpatient clinics in Deyang region was investigated.

Aim 2: To collect air pollution indicators including PM2.5, PM10, NO_2_, and SO_2_ in Deyang area and discuss the correlation between pollutants and the prevalence of AR.

Aim 3: To understand the quality of life of AR patients in the Asia-Pacific region via analyzing the correlation between AR symptoms and atmospheric pollutants.

Aim 4: To provide targeted guidance and Suggestions for government departments to prevent airway inflammation and other diseases caused by air pollution. In this way, medical expenses of the public and health departments can be reduced and the quality of life of patients can be improved.

### Study registration

2.2

The protocol scheme matches PRISMA's reporting standards. This study protocol has been registered on Chinese Clinical trial registry (http://www.chictr.org.cn/index.aspx) with a unique ID of ChiCTR2000029027.

### Participants

2.3

All age groups (newborn to adult) suffering from any form of AR will be included. These may include participants with acute or chronic comorbidities but without immunodeficiency. Participants may also include those on conventional treatment for other health issues. Symptoms of AR include rhinorrhea, nasal obstruction, nasal itching, and sneezing which are reversible spontaneously or with treatment. A diagnosis of AR will include the following symptoms based on the Guideline Summary of Management of Allergic and Non-AR: Nose: nasal discharge (runny nose), sneezing, nasal blockage or congestion, and itchy nose and palate; Eye: bilateral itchy eyes, red eyes (concomitant allergic conjunctivitis), and swollen eyes.

There is no specific duration of symptoms required for diagnosis; however, a very short or nonrepetitive history of symptoms generally excludes a diagnosis of AR. The presence of any one of the nasal symptoms will be essential for a diagnosis of AR except when nasal blockage is the only symptom. Nasal blockage on its own rarely indicates allergy. The duration of symptoms will not be present as a criterion since this has not been defined for a diagnosis of AR.

#### Inclusion criteria

2.3.1

All participants will be diagnosed as AR in accordance with the diagnosis and treatment guidelines for AR (2015, Tianjin), and will be diagnosed by a senior attending physician who had received unified training. All the patients participating in the questionnaire can understand the questionnaire accurately and cooperate with the successful completion of the questionnaire survey.

#### Exclusion criteria

2.3.2

The exclusion criteria are as follows: Patients with nasal infection, nasal polyps, nasal tumors, mental disorders, and immunodeficiency will be excluded.

#### Recruitment

2.3.3

Patient data will be collected for all patients with AR, including general data such as sex, age, sex, place of residence, course of disease, and main clinical symptoms.

### Study areas

2.4

Deyang is the North city of Sichuan Province and closed to Sichuan capital city Chengdu. In recent years, PM pollution has become a serious issue for this city due to its large population and automobile and industrial emissions.

### Data collection

2.5

Each area in Deyang city (including Jingyang, Shifang, and Mianzhu city of Sichuan Guanghan, Luojiang district, and Zhongjiang county) outpatient department of otolaryngology head and neck surgery patients, according to the guide to conform to the diagnosis and treatment of AR (2015, Tianjin) for inclusion criteria, the general clinical data (including gender, age, duration, attack frequency, main symptom, etc) each year, Deyang area in patients with AR disease registration rates.

Air pollution levels of ambient air pollutants including PM2.5, PM10, sulfur dioxide (SO_2_), nitrogen dioxide (NO_2_), carbon dioxide (CO), and O_3_ will be derived from the China National Environmental Monitoring Center (http://www.cnemc.cn/). Daily data of weather conditions, including relative humidity (%) and mean temperature (°C), will be obtained from the China Meteorological Monitoring Database (http://data.cma.cn/).

### Statistical plan

2.6

Continuous variables will be expressed as mean ± standard deviation, while nominal variables are expressed in frequency and percentage. Comparisons of continuous variables will be performed using the 2-tailed *t* test for unpaired samples or Welch *t* test as appropriate. Comparisons of nominal variables will be performed using the Chi-squared test or Fisher exact test as appropriate. Multivariate logistic regression test will be used to evaluate the association between predictor variables and outcome variables. Statistical significance will be defined by a *P* value of <.05. The statistics will be performed using SAS 9.4 (SAS Institute Inc, Cary, NC).

The data used for the study will be preserved and analyzed by the primary investigator. The data are accessible only to the primary investigator and study nurse for data safety. The data will be preserved for 2 years after the end of the study.

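### Section 2.6 names only tests that in standard form treat patients as independent, although pollution is a group-level value shared between patients; if outcomes cluster, P values for patient-level pollutant associations are likely too small

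*Protocol article*

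**What the plan says.** Section 2.6 (Statistical plan) names every inferential method in the article:

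- Continuous variables: "Comparisons of continuous variables will be performed using the 2-tailed" *t* "test for unpaired samples or Welch" *t* test.
- Nominal variables: "Comparisons of nominal variables will be performed using the Chi-squared test or Fisher exact test as appropriate".
- Associations: "Multivariate logistic regression test will be used to evaluate the association between predictor variables and outcome variables".

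Significance is set at P below .05 and the software is SAS 9.4. The section names no random effect, robust variance, generalised estimating equation (GEE) or time-series structure.

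Section 2.5 (Data collection) takes patients from ear, nose and throat outpatient departments across the region: "Each area in Deyang city (including Jingyang, Shifang, and Mianzhu city of Sichuan Guanghan, Luojiang district, and Zhongjiang county". This lists six areas. Pollutant levels "will be derived from the China National Environmental Monitoring Center", so exposure is not measured per person. Weather is given a time resolution ("Daily data of weather conditions, including relative humidity (%) and mean temperature (°C"), but pollution is not. The article does not say whether a patient is linked to pollution by day, month or year.

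Aim 3 in section 2.1.1 relates symptoms to pollutants. The Discussion paragraph of the abstract promises correlations with patient-level outcomes, "including symptom score, drug score, quality of life score, asthma control score, side effects", and with laboratory results.

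**The concern.** The exposure varies between groups of patients and the outcomes are recorded per patient. Patients linked to the same area and period carry the same pollutant value. They are also likely to share season, weather, clinic and assessor. Where that leaves their outcomes positively correlated, the group holds less information about the pollutant effect than its head count suggests. A test that counts every patient as independent then gives standard errors that are too small.

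There is also a problem of fit. The stated interest is in scores against pollutant concentrations, both in principle continuous. A *t* test needs two groups, a chi-squared test needs categories on both sides, and logistic regression needs a categorical outcome. To use them, a score or a pollutant must be cut into categories, which discards information.

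Aim 4 is to guide government departments, so overstated significance for a pollutant could carry into policy advice.

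**Working it through.** **Stated figure.** There is none to reproduce. The article gives no sample size, power, cluster size or ICC; only the 0.05 threshold is stated.

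**Inputs from the article.** Six areas (section 2.5). January 2019 to December 2020 (section 2.1.1), which is 365 + 366 = 731 days, so at most 6 × 731 = 4,386 area-days. Two-sided alpha 0.05, so the critical value is 1.96.

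**Assumptions, not in the article.** *m* patients per shared exposure value, and ICC (residual correlation within that group, after covariates) from 0 to 0.10.

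**Formulas.** With exposure constant within equal-sized groups:

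- Design effect DE = 1 + (*m* − 1) × ICC
- True error of a naive 5% test = 2 × [1 − Φ(1.96 / √DE)]

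Example: *m* = 20 and ICC = 0.05 give DE = 1 + 19 × 0.05 = 1.95, and 2 × [1 − Φ(1.96 / √1.95)] = 16.0%.

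| *m* | ICC 0 | ICC 0.02 | ICC 0.05 | ICC 0.10 |
|---|---|---|---|---|
| 2 | 5.0% | 5.2% | 5.6% | 6.2% |
| 5 | 5.0% | 5.9% | 7.4% | 9.8% |
| 10 | 5.0% | 7.1% | 10.4% | 15.5% |
| 20 | 5.0% | 9.5% | 16.0% | 25.0% |
| 50 | 5.0% | 16.4% | 29.1% | 42.0% |

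**Check by simulation under no effect.** Welch *t* and chi-squared compared high-exposure with low-exposure groups; the logistic score test used continuous exposure. The binary outcome proportion was assumed to be 0.3.

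| Setting | ICC | Welch *t* | Chi-squared | Logistic |
|---|---|---|---|---|
| 731 days, *m* = 20 | 0 | 5.2% | 4.8% | 4.7% |
| 731 days, *m* = 20 | 0.02 | 8.6% | 8.5% | 9.4% |
| 731 days, *m* = 20 | 0.05 | 14.9% | 15.9% | 14.2% |
| 731 days, *m* = 20 | 0.10 | 25.2% | 25.3% | 26.7% |
| 731 days, *m* = 5 | 0.10 | 9.3% | 9.6% | 9.3% |
| 12 area-years, *m* = 50 | 0.02 | 16.2% | 17.1% | 16.3% |
| 12 area-years, *m* = 200 | 0.02 | 37.7% | 37.6% | 37.2% |

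The simulations agree with the formula and show three things. A shared exposure alone, with ICC 0, does not inflate the error. With few patients per exposure value the inflation is small. If exposure is assigned by area and year, it is large even at a low ICC. Neither calculation includes correlation between successive periods.

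**Fit of method to question.** The Methods paragraph of the abstract mentions a correlation analysis, and Aims 2 and 3 use the same term. Section 2.6 does not include one. A standard correlation coefficient would suit two continuous variables, but its test also assumes independent pairs, so it would not resolve the first problem.

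**The case against.** The strongest reply is that several steps in the argument are not in the article.

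- **Linkage.** A reader might infer that patients are linked to pollution by area and day. Only the weather data are called daily, and section 2.5 also speaks of yearly registration. This stands: the linkage unit is unstated.
- **Certainty.** A reader might conclude that P values must be too small. That also requires positive residual correlation, and temperature and humidity, which are collected, could absorb part of it in a multivariate model. This stands: the error remains 5% at ICC 0.
- **Size.** A reader might take 9.5% to 25% as the effect. That is a single row of the table, *m* = 20. Twenty patients on each of 4,386 area-days would be 87,720 records if every calendar day counted, and the article suggests no such volume. This stands.
- **Repeat visits and median splits.** A reader might assume that patients attend repeatedly, or that scores will be split at the median with a calculable loss. The study is called cross-sectional, no repeat measurement is scheduled, and no cut-point is planned. Neither reading is supported.
- **Scope of the tests.** The *t* and chi-squared tests may be meant only for descriptive comparisons, the logistic regression could be a clustered form, and an ordinal logistic model could take a score. These readings are possible, but the article does not state any of them.

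The last line of defence is that a condensed article leaves clustering to a fuller document. It does not succeed here. Section 2.6 makes a specific choice of methods, and a plan that followed it as written would carry the problem forward.

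**Conclusion.** The point holds in conditional form. The methods in section 2.6 in standard form treat patients as independent, while exposure is a group-level value from public monitors. If outcomes are positively correlated within the groups that share an exposure value, after covariates, P values for pollutant associations with patient-level outcomes are likely too small. Shared season, weather and clinic make that plausible, but the article does not establish it.

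The size is unknown. Under the assumed ICC of 0 to 0.10 it runs from no inflation to a true error of about 6% at 2 patients per exposure value, 10% at 5 and 25% at 20, with more under coarser linkage such as area-year.

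The mismatch between the named tests and continuous pairs needs no assumed ICC or cluster size. It follows from the wording of section 2.6 wherever the scores and pollutants are analysed as continuous.

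The point is confined to pollutant associations with patient-level outcomes. Comparisons of patient characteristics that vary within an area and period are much less affected. It should be corrected before analysis, but it does not call the data collection into question.

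**What to change.** For pollutant associations with patient-level outcomes, replace the tests in section 2.6 as follows:

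1. State the unit at which patients are linked to pollution (area and day, month or year).
2. Fit a regression suited to the outcome on continuous pollutant level: linear or ordinal for scores, logistic for binary outcomes. Include fixed area effects and adjust for season, temperature, humidity, age and sex.
3. Allow for the shared exposure unit with either a random effect or a cluster-robust or GEE variance at that level. Both together at the same level are redundant.
4. Allow for serial correlation between successive periods, which step 3 alone does not cover.
5. Add a patient effect only if repeat visits are recorded.
6. Keep *t* and chi-squared tests for descriptive comparisons of patient characteristics.

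If linkage turns out to be by area-year, there are only 6 × 2 = 12 exposure values. Six area effects then leave little contrast, and robust variances are unreliable with so few groups. Step 1 therefore has to be settled first.

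The cost is a change of wording, slightly more analysis work in the SAS 9.4 already specified, and wider intervals. Steps 2 to 4 use variables the article already plans to collect.

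### Only patients with allergic rhinitis are enrolled, but the main aim and Aims 1 and 2 concern AR risk and prevalence, with no defined denominator and no model that fits them

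*Protocol article*

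**What the plan says.** The main aim (section 2.1) reads "We aim to clarify the relationship between air pollution exposure and the risk of AR". Under Special aim (2.1.1), Aim 1 is that "the prevalence of AR in outpatient clinics in Deyang region was investigated", and Aim 2 is to "discuss the correlation between pollutants and the prevalence of AR". Aim 3 is different in kind: it concerns AR symptoms and quality of life among patients.

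The population is described consistently, and always as AR only. Participants (2.3) states "All age groups (newborn to adult) suffering from any form of AR will be included". Inclusion criteria (2.3.1) states "All participants will be diagnosed as AR in accordance with the diagnosis and treatment guidelines for AR". Recruitment (2.3.3) states "Patient data will be collected for all patients with AR". The Abstract says the same. No outpatient without AR, control group or population sample is mentioned.

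Data collection (2.5) refers to yearly AR registration rates from otolaryngology outpatient departments in the areas of Deyang, without saying what the cases are divided by. It describes the weather data as daily and gives no time resolution for the pollutants.

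The Statistical plan (2.6) lists t tests, chi-squared or Fisher tests, and one association model: "Multivariate logistic regression test will be used to evaluate the association between predictor variables and outcome variables". It names neither outcomes nor predictors. The Abstract also promises a correlation analysis of pollutants with AR risk.

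**The concern.** Risk and prevalence are both fractions. The numerator is people with AR; the denominator must also count people, attendances or person-time without AR. The enrolment rules supply only the numerator. If the denominator is not collected from elsewhere, the study cannot say whether AR is more frequent when or where pollution is higher.

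The statistical plan does not close the gap. A logistic regression on the enrolled patients can compare one kind of AR patient with another, for example more against less symptomatic. An odds ratio from that model describes severity among people who have the disease. With the outcome unnamed and the main aim worded as risk, such a result could easily be reported as an effect on AR risk, which it is not. The outcome might also be chosen after the data have been seen.

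**Working it through.** The article states no sample size, effect size or power, so there is no figure to reproduce. The check is whether the stated data and model identify the stated quantities.

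**Step 1: match each aim to its data and model.**

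| Aim | Quantity needed | Data stated | Model stated |
|---|---|---|---|
| Main aim | AR risk by pollution level | AR patients only | Logistic regression, outcome unnamed |
| Aim 1 | AR prevalence in outpatient clinics | AR patients; registration rates without denominator | None for a rate |
| Aim 2 | Prevalence against pollutant level | As for Aim 1 | None for a rate, count or time series |
| Aim 3 | Symptoms and quality of life against pollutants | AR patients | Logistic regression can serve, once an outcome is named |

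Only Aim 3 has data and a model that fit each other.

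**Step 2: what case counts alone say.** Assume 500 AR cases at high exposure and 500 at low exposure. With denominators N1 (high) and N0 (low), the odds ratio is [500/(N1 − 500)] / [500/(N0 − 500)].

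- N1 = 2500, N0 = 2500: (500/2000)/(500/2000) = 1.00
- N1 = 2000, N0 = 3000: (500/1500)/(500/2500) = 0.333/0.200 = 1.67
- N1 = 3000, N0 = 2000: (500/2500)/(500/1500) = 0.200/0.333 = 0.60

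The cases are the same in all three lines, yet the association is null, positive or negative. Counts and denominators are assumed; the article gives none.

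**Step 3: what a denominator restores.** In simulated data with an assumed 20,000 subjects and a true odds ratio of 1.2 per standard deviation of exposure, a logistic model that included the non-AR subjects gave these estimates at three prevalences across the 4% to 38% range in the Introduction:

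- 4%: 1.23 (95% CI 1.15 to 1.33)
- 20%: 1.24 (1.20 to 1.29)
- 38%: 1.20 (1.17 to 1.24)

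Logistic regression is therefore not the fault in itself. What is missing is anyone to contrast with the cases.

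**Step 4: what the registration rates could offer.** Data collection can be read as naming six areas, and Aim 1 covers January 2019 to December 2020, which is two calendar years. Yearly rates would then give at most 6 × 2 = 12 area-year values. These are contrasts over place and time, but they become prevalences only with a denominator, and section 2.6 has no model for them.

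**The case against.** The strongest reply is that the article never makes AR status the logistic outcome. The Abstract lists outcomes that vary within AR patients (several clinical scores, nasal function, serum immunoglobulin E), and Aim 3 relates symptoms to pollutants. The planned tests can be run on these. That stands. A reader might infer that the planned regression must fail because every record has the same outcome. A logistic model with a constant outcome indeed has no finite estimate, but the article does not specify that model, so non-convergence cannot be charged to the plan. What remains is that the models which can be fitted do not answer the main aim or Aims 1 and 2.

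Second, the registration rates, the several areas and the two-year window point towards an aggregate analysis, and the Abstract mentions correlation. This also stands in part. A reader might infer that the study has no contrast in time or place at all, and the article does not support that. It does leave the denominator undefined and the rate analysis without a model.

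Third, the article is a condensed account, and a full protocol or analysis plan might say more. Such a document could refine a model or name outcomes. It cannot produce non-AR records while the inclusion criterion requires AR of every participant. The conflict is between statements that the article itself makes.

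Finally, because disease duration is recorded, a reader might infer that pollution in 2019 to 2020 comes too late to explain AR that began earlier. That would count against a claim about incidence. The title and Aims 1 and 2 concern prevalence in a cross-sectional study, where existing disease is what is counted, so this is not part of the point.

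**Conclusion.** The point holds in this form: an AR-only population, an undefined denominator for the registration rates, and no stated model for a rate, count or time series together leave the main aim and Aims 1 and 2 without a valid estimator. For those aims the gap is complete and does not depend on sample size; for Aim 3 it does not arise. It should be settled before analysis.

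The conclusion rests on reading the Abstract and sections 2.3 to 2.3.3 at face value, and on no denominator being defined in section 2.5. If clinic totals are in fact being collected, the defect for Aims 1 and 2 shrinks to a missing definition and a missing model. The 1.67, 1.00 and 0.60 in the working are illustrations with assumed counts, not predictions for this study.

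**What to change.** **Main aim.** Restate it as the short-term association of air pollution with AR outpatient attendance, and replace the logistic model for this aim with a time-stratified case-crossover. Each patient's visit day is compared with the other days of the same weekday, month and area, by conditional logistic regression on lagged pollutant level, adjusted for daily temperature and humidity. Patient i contributes exp(βx_visit + γz_visit) / Σ_j exp(βx_j + γz_j), where x is the lagged pollutant level, z is the weather, and the sum runs over the visit day and its comparison days. Each case supplies its own contrast, so no non-AR patients are needed.

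**Aims 1 and 2.** Either define the denominator, for example all otolaryngology outpatient attendances per area and period from clinic counts, and fit a count or rate model with the log of that denominator as offset; or drop the prevalence claim.

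**Logistic regression.** Keep it for named outcomes within AR patients (Aim 3), and do not report its results as AR risk.

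**Cost.** Recruitment is unchanged. The visit date must be recorded, since it is not among the listed variables, and pollutant data must be obtained at daily resolution, which the article states only for weather. The denominator option needs clinic totals by area and period. The main downside is the change of estimand: the case-crossover result concerns what triggers attendance, not the development or prevalence of AR, and it does not by itself deliver Aims 1 and 2.

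### Every participant has AR and no denominator is defined, so the one regression in section 2.6 cannot estimate an association between pollution and AR status

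*Protocol article*

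**What the plan says.** All references are to the protocol article.

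- **Target.** Section 2.1 states: "We aim to clarify the relationship between air pollution exposure and the risk of AR". Aim 2 in section 2.1.1 is to "discuss the correlation between pollutants and the prevalence of AR".
- **Sample.** Section 2.3: "All age groups (newborn to adult) suffering from any form of AR will be included". Section 2.3.1: "All participants will be diagnosed as AR". Section 2.3.3: "Patient data will be collected for all patients with AR". No section describes people without AR. Aim 1 speaks of prevalence in outpatient clinics and section 2.5 of registration rates, but neither says what the numerator is divided by, and non-AR visits are not collected.
- **Model.** Section 2.6: "Multivariate logistic regression test will be used to evaluate the association between predictor variables and outcome variables". Outcomes and predictors are not named, and no matching or strata are mentioned. The other tools there are descriptive summaries, t and Welch tests, and chi-squared and Fisher tests.
- **Other analyses mentioned.** The methods paragraph of the abstract promises a correlation analysis of pollutants with AR risk, without a method. The abstract's discussion paragraph lists symptom, drug, quality-of-life and asthma-control scores, side effects and laboratory tests as things to be related to pollutants.
- **Exposure data.** Section 2.5 takes pollutants from the national monitoring centre without stating a time resolution. For weather it specifies "Daily data of weather conditions".

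**The concern.** A logistic model for a disease compares people who have it with people who do not. Here entry to the study requires the disease. The stated target, the stated sample and the one stated regression therefore do not fit together. A later analysis plan can add covariates or lags, but it cannot make AR status vary in a sample fixed as AR patients only.

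If this stands, whoever analyses the data must choose an outcome, a comparison group or a different model after the data are in. The result would not be a pre-planned answer to the main aim.

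**Working it through.** The article gives no sample size, effect size or event count, so there is no figure to reproduce. The check is whether the model can be estimated, first as named and then in a form that uses cases alone.

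**1. Logistic regression with AR status as outcome.** Take section 2.6 as the ordinary unconditional model, the natural reading when no strata are named. With pollutant x, intercept a and slope b, each record with y = 1 contributes −log(1 + exp(−(a + bx))). Sections 2.3 to 2.3.3 make y = 1 for everyone, so

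log L = −Σ log(1 + exp(−(a + bx))).

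This rises towards 0 as a grows, whatever b is. With 1,000 records (an assumed number), a = 20 and b = 0:

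1,000 × log(1 + e^−20) ≈ 1,000 × 2.06 × 10^−9 ≈ 2 × 10^−6.

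The negative log-likelihood is about 2 × 10^−6 for all slopes from −0.5 to 0.5, so the data do not tell them apart. The standard error of b at increasing intercepts is:

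| Intercept | SE of slope |
|---|---|
| 5 | 0.35 |
| 10 | 4.2 |
| 15 | 52 |
| 20 | 631 |

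Each step of 5 multiplies it by about e^2.5 ≈ 12, without limit. A trial fit to 500 all-case records did not converge (intercept 26 with SE 648, slope 5.6 with SE 202). The number of patients does not matter: more cases add more ones.

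**2. A case-only alternative.** In a time-stratified case-crossover analysis, each AR visit is compared with the other days of the same weekday, month and year in the same area. A visit contributes

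exp(b·x_visit) / Σ exp(b·x_day), summed over the days of its stratum.

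The comparison is between days within a case, so no AR-free person is needed.

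Control days over January 2019 to December 2020 (the period in Aim 1; 365 + 366 = 731 days): in a month of 28 + r days, r weekdays occur five times and 7 − r occur four times. Summed over the days of the month, the number of control days is

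5 × 4 × r + 4 × 3 × (7 − r) = 84 + 8r.

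That is 108 for a 31-day month, 100 for a 30-day month, 84 for February 2019 and 92 for February 2020.

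- 2019: 7 × 108 + 4 × 100 + 84 = 1,240
- 2020: 7 × 108 + 4 × 100 + 92 = 1,248
- Total 2,488; 2,488 / 731 = 3.40 per day, minimum 3, maximum 4

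**3. Does it return an estimate?** Two simulations were run. Visit numbers, effect sizes and pollutant series are all assumptions.

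- With 500 to 2,000 visits and 200 replicates per setting, assumed odds ratios of 1.0, 1.1 and 1.2 gave mean estimates of 1.00, 1.10 and 1.20. With no effect, the rejection rate was 4 to 5.5% at the 0.05 level.
- With about 4,900 visits, opposing seasonal cycles and a weekend dip, the mean log rate ratio per 10 µg/m³ was −0.004 when the truth was 0, and 0.026 when it was 0.030. The second is a shortfall of 0.004 / 0.030 ≈ 13%, which I have not explained. In the no-effect setting a plain correlation averaged r = −0.29, a value produced by the seasonal cycles put in.

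These runs show that the model can be fitted to cases alone. They give neither this study's power nor its bias.

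**The case against.** Section 2.6 does not name AR status as the outcome. It speaks of outcome variables in general, and the abstract and Aim 3 announce outcomes that vary among AR patients. Logistic regression works for any of these once binary, and the two-group tests work for groups such as sex or area. Assigning outcomes to models is commonly left to an analysis plan. All of this stands. A reader might infer that section 2.6 can deliver nothing, or that modelling a within-AR outcome would be improvised; the documents do not support either. But these outcomes serve Aim 3, not the main aim in section 2.1.

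The article does mention a correlation analysis for AR risk and prevalence. That is true, but no method or unit of analysis is given, and section 2.6 does not take it up.

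Aim 1 and the registration rates hint at a clinic denominator. With one, AR versus other attendances could be modelled by grouped logistic regression. That is correct, so the problem is tied to the missing denominator as well as to the model. No section defines the denominator, though.

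A reader might also infer that a case-crossover analysis repairs the main aim by a change in section 2.6 alone. It does not. It replaces the question by short-term triggering of visits, and AR is a chronic disease by the article's own account, so a visit date need not mark onset.

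**Conclusion.** The point holds within limits. For the main aim, the only regression named cannot estimate an association with AR status in the sample as described. This follows from the form of the likelihood and does not depend on sample size. It rests on two readings: that the logistic model is unconditional, and that AR status is the outcome meant for the main aim.

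It does not extend to outcomes that vary among AR patients, for which logistic regression remains suitable. Nor do the simulations measure how wrong this study's results would be; in particular, r = −0.29 follows from assumed seasonal patterns and concerns correlation, not the logistic model.

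The correction is needed before analysis, because otherwise the outcome, comparator or model for the main aim is left to be chosen after the data are seen.

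**What to change.** **Section 2.6.** Replace the logistic sentence with text such as: *The association of daily pollutant levels with AR attendance will be estimated by a time-stratified case-crossover analysis (conditional logistic regression). Pollution on and just before the visit day is compared with days of the same weekday, month and year in the same area, adjusted for daily temperature and relative humidity. Results are odds ratios per fixed pollutant increment with 95% confidence intervals. Ordinary logistic regression is used only for binary outcomes that vary among AR patients.*

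**Sections 2.3.3 and 2.5.** List the visit date as a data item; prospective clinic enrolment implies one, but it is not named. State that pollutant values are obtained daily.

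**Sections 2.1 and 2.1.1.** Reword the aim that this analysis serves to short-term triggering of AR attendance. For Aims 1 and 2, define a denominator, for example all attendances at the participating clinics, or state that prevalence will not be estimated. Either specify the correlation analysis or remove it.

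**Cost.** Edits to the text, one added data field, confirmation of the pollutant resolution and modest extra analysis in the SAS version already named. The case-crossover part needs no additional participants; place of residence and daily weather are already planned. Its downside is that it says nothing about prevalence or long-term risk, and the visit-date limitation for a chronic disease should be stated with the results. A denominator for Aims 1 and 2 would be further data collection.
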